#### *11.6.2 Potential study benefits*

Participation may increase their awareness of pain management, prescription opioid use and disposal. This is a low risk study and we believe the aforementioned risks are reasonable compared to the direct benefits.

#### *11.6.3 Risk/benefit assessment*

Anticipated risks of this study should be minimal and the risk/benefit ratio is very favorable.

**Q2:**

*We wanted to see how you are doing after your recent procedure. We may check in a few times.*

*[line break] How would you rate your pain over the past 24 hours? (from 0-10, 0 being no pain [please choose one number])."*

LOGIC:

- If response  $\neq$  0-10  $\rightarrow$  REPLY "I'm sorry. We don't understand. Please text back a number 0-10."
- If no response in 3 hours  $\rightarrow$  REPLY "We missed your response. How would you rate your surgical pain over the past 24 hours? (from 0-10, 0 being no pain [please choose only one number])."

**Q3:**

*"We encourage you to contact your provider if your pain is too much to handle.*

*[line break] How have you been able to manage your pain since being home? From 0-10, 0 being not at all able [please choose one number]."*

LOGIC:

- If response = 0-10  $\rightarrow$  Proceed to **Q4**
- If response  $\neq$  0-10  $\rightarrow$  REPLY "I'm sorry. We don't understand. Please text back a number between 0-10."
- If no response in 3 hours  $\rightarrow$  REPLY "We missed your response. How have you been able to manage your pain since being home? From 0-10, 0 being not at all able [please choose one number]."

**Q4:**

*"We just have a few more questions. [line break] Have you taken any of the following medications for your pain since your procedure (Acetaminophen, Aspirin, Ibuprofen, or Naproxen)? [Y for yes or N for no]. "*

326 LOGIC:

327 ○ If response = Y, N, yes, or no → Proceed to **Q5**

328 ○ If response ≠ Y, N, yes or no → REPLY "I'm sorry. We don't understand. Please text back Y or N."

329

330 **Q5:**

331 *"Thanks, this information helps guide our practice. It looks like you were also prescribed [opioid\_RX] for your*

332 *pain. [line break]Have you taken this medication? [Y for yes or N for no]."*

333

334 LOGIC:

335 ○ If response = Y or yes → Proceed to **Q6**

336 ○ If response = N or no → Proceed to **Q10**

337 ○ If response ≠ Y, N, yes or no → REPLY "I'm sorry. We don't understand. Please text back Y or N."

338

339 **Q6:**

340 *"Can you estimate how many pills of [opioid\_RX] you have taken since your procedure? Please text back a*

341 *number"*

342 LOGIC:

343 ○ If response = Number → Proceed to **Q7**

344 ○ If response ≠ Number → REPLY "I'm sorry. We don't understand. Please text back a number."

345

346

347 **Q7:** *"Do you have any of these pills remaining? [Y/N]"*

348 LOGIC:

349 ○ If response = Y, yes → Proceed to **Q8**

350 ○ If response = N, no Proceed to **Q10**

351 ○ If response ≠ Y, N, yes or no → REPLY: *"I'm sorry. We don't understand. Please text back Y or N."*

352

353

354 **Q8:** *"Do you plan to continue taking [opioid\_RX] to control your pain? [Y/N]"*

355 LOGIC:

356 ○ If response = Y or yes → REPLY: *"Thanks so much for your feedback! We'll check back with you in a few*

357 *days. If you have any questions or concerns about your care or health please contact your surgical team.*

358 *Have a nice day!"*

359

360 ---This patient will be texted in 1 week---

361

362  
363  
364  
365  
366  
367  
368  
369  
370  
371  
372  
373  
374  
375  
376  
377  
378  
379  
380  
381  
382  
383  
384  
385

- If response = N or no → **Move to Q9**
- If response ≠ Y, N, yes or no → REPLY: *"I'm sorry. We don't understand. Please text back Y or N."*

**Q9:** "Have you disposed of your unused %opioid% medication? [Y/N]"

LOGIC:

- If response = Y or Yes → That's great to hear. It's important to dispose of your unused medication. Just one more question for you: [line break] *"How many days did it take for your pain to improve after your procedure? Please text back a number."*
- If response = N or No → It's important to dispose of your unused medication. Penn pharmacies will take them back. Find locations here: <https://bit.ly/2VQPekA>. [line break] Just one more question for you: *"How many days did it take for your pain to improve after your procedure? Please text back a number."*

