## 3. Aims

### *3.1 Primary outcome*

The primary outcome variable is rate of self-reported opioid disposal.

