## **8. Study procedures**

### *8.1 Consent*

Upon recruitment, individuals will be sent a text message via the Way to Health platform with an opportunity to consent or decline. Participants have the ability to opt-out of text messaging and the study at any point by text messaging a response of “STOP.” The current post-operative text messaging protocol has been approved by the QI IRB and has been in place with an average response rate of 50-60%. We will not change the questions or timing of messages being sent. The questions related to opioid disposal are pre-existing.

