### *8.2 Procedures*

After providing informed consent, participants will be sent messaging on post-operative days 4, 7, 14, 21, and 28. At each time point, patients are asked to self-report pain intensity (scale 0-10, 10 being severe), ability to manage pain (scale 0-10, 10 being very able to manage), and use of non-opioid and opioid analgesics. Patients who are using opioid analgesics are asked to report quantity used, projection of future use for acute pain. Patients reporting no further use are asked about disposal (Yes or No).

Patients will be mailed opioid disposal packets, DispoRx, which are small chemical polymers which individuals can pour directly into a pill bottle. The individual shakes the bottle and the medication is deactivated, rendered unusable and can be placed safely in the trash. We will mail these packets to individuals within the first 7 days for Orthopedic and Urology and timed for 21 days for Neurosurgery.

145 Participants will be randomly assigned at the individual level to receive a disposal packet. Participants  
146 randomized to the control arm will receive no other interventions.

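### The text-message script cannot record disposal for patients who took no opioid, or for patients who truthfully report no pills left because they disposed of them

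*Supplement*

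**What the plan says.** Section 3.1 sets a single primary outcome: "The primary outcome variable is rate of self-reported opioid disposal". It gives no denominator.

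The text-message script at the end of the protocol contains one disposal item, Q9: "Have you disposed of your unused %opioid% medication? [Y/N". The routing around it is:

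- Q5 (has the prescribed opioid been taken): "If response = N or no → Proceed to Q10".
- Q7 asks "Do you have any of these pills remaining? [Y/N", and then: "If response = N, no Proceed to Q10".
- Q8 (plan to continue): "If response = N or no → Move to Q9". A yes ends the exchange, and the patient is texted again in a week.

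Q10 asks only how many days it took for pain to improve.

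Section 8.2 describes who is asked in one line: "Patients reporting no further use are asked about disposal (Yes or No"). It schedules messages on days 4, 7, 14, 21 and 28 and says the questions are put at each time point. Section 8.1 fixes the instrument: "We will not change the questions or timing of messages being sent". Section 9 does not say how a participant who never reaches Q9 is counted.

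**The concern.** Two groups never reach the disposal question.

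**Never-takers.** An acute opioid prescription is an inclusion criterion (section 5.5). A patient who took none of it may hold the whole supply, or may have disposed of it. Neither state is recorded.

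**Complete disposers.** Q7 does not separate having used all the tablets from having already disposed of them. A patient must say that pills remain before being asked whether they were disposed of. Section 8.2 describes the kit as deactivating the tablets in the bottle, which then goes in the trash, so a literal answer at the next message is that none remain. Repeating the same script does not recover the event: a patient who answers no at Q9 on one day and then disposes is routed past Q9 the next time.

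The instrument for the only primary outcome can therefore miss the event that the kit is meant to produce. The recorded rate would be wrong in both arms, and the missing answers could not be reliably reconstructed afterwards.

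**Working it through.** **1. Paths through the script.** There are four valid combinations of Q5, Q7 and Q8.

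| Q5 | Q7 | Q8 | Ends at |
|---|---|---|---|
| No | – | – | Q10, disposal not asked |
| Yes | No | – | Q10, disposal not asked |
| Yes | Yes | Yes | Exit, texted again in a week |
| Yes | Yes | No | Q9, disposal asked |

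One of the four reaches Q9.

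**2. The plan's power figure.** Inputs from section 5.4: 125 per arm, baseline 25%, a change of 20%, two-sided alpha 0.025, at least 80% power. The change is read as 20 percentage points (25% vs 45%), because 25% vs 30% would give only 8.7% power.

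Power = Φ[(d − z·SE0)/SE1], where z = 2.2414, SE0 uses the pooled rate and SE1 the separate rates.

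- Pooled rate 0.35: SE0 = √(0.35 × 0.65 × 2/125) = 0.0603.
- SE1 = √(0.25 × 0.75/125 + 0.45 × 0.55/125) = 0.0590.
- Power = Φ[(0.20 − 2.2414 × 0.0603)/0.0590] = 86.4%.

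The plan's statement holds when every disposal is captured.

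**3. Disposers lost at Q7.** Let f be the share of true disposers who answer no at Q7, equal in both arms. The documents give no value, so f is an assumed range.

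- *Counted as not disposed:* recorded rates are 0.25(1 − f) and 0.45(1 − f), still over 125 per arm.
- *Dropped:* recorded rates are p(1 − f)/(1 − pf), over 125(1 − pf) per arm, with p = 0.25 or 0.45.

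| f | Counted as not disposed | Difference (points) | Power | Dropped | Difference (points) | Power |
|---|---|---|---|---|---|---|
| 0 | 25.0% vs 45.0% | 20.0 | 86.4% | 25.0% vs 45.0% | 20.0 | 86.4% |
| 10% | 22.5% vs 40.5% | 18.0 | 79.9% | 23.1% vs 42.4% | 19.3 | 83.6% |
| 20% | 20.0% vs 36.0% | 16.0 | 72.1% | 21.1% vs 39.6% | 18.5 | 80.2% |
| 30% | 17.5% vs 31.5% | 14.0 | 63.2% | 18.9% vs 36.4% | 17.5 | 75.8% |
| 50% | 12.5% vs 22.5% | 10.0 | 43.6% | 14.3% vs 29.0% | 14.7 | 63.5% |

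**4. Unequal loss.** If 80% of disposals are captured in control and 60% in the kit arm, with the rest counted as not disposed, the recorded rates are 0.25 × 0.8 = 20% and 0.45 × 0.6 = 27%. A true difference of 20 points is recorded as 7, with 17.4% power.

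**5. Never-takers excluded.** If 10%, 20% or 30% of each arm took no opioid and the rates among the rest are unchanged, 112.5, 100 or 87.5 per arm can be asked. Power is 82.2%, 77.0% or 70.7%. These shares are also assumptions.

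**The case against.** **Section 8.2 may agree with the script.** A reader might infer a flat contradiction. The documents do not support that. The disposal sentence directly follows one about patients using opioids and their projected future use, which is Q8, and a no at Q8 does lead to Q9. Read more broadly, the sentence covers never-takers and complete disposers too. It is ambiguous. On the narrow reading, however, the outcome leaves out both groups without saying so.

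**The 25% may already be a recorded rate.** Section 8.1 says the disposal questions were in use before the trial. If the preliminary 25% came through this script, scaling it down again counts the loss twice. A reader might take the fall from 86% to 44% as the expected damage. That figure needs half of all disposers to be lost, all of them counted as not disposed, and 25% to be a true rate, and the documents establish none of these. The point about validity still stands: an undercount in the historical baseline does not show that capture will be equal in the kit arm.

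**Bias toward zero is not general.** The risk difference shrinks under equal loss. If unasked patients are dropped, the odds ratio stays at 2.45 for every f in the table, and the risk ratio rises from 1.80 to 2.03 at f = 50%. The plan names no effect measure. Nor is there a stated reason for the Q5 skip to differ by arm.

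**Later scripts may differ.** Only one script is shown, its first item is not, and its opening reads like a first contact. A no at Q7 on day 4 cannot come from a kit mailed after day-4 consent. But section 8.2 says the questions are put at each time point, which supports reuse. Some patients may also answer Q7 loosely and still reach Q9.

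**Changing the routing could confound the comparison.** Section 9 words the primary comparison as baseline against the 6-week period, and a changed instrument would spoil that. This does not defeat the fix in a design that section 5.1 states as two-arm and randomized, provided that both concurrent arms get the same routing.

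**Conclusion.** The point holds. As written, the script never asks never-takers about disposal and does not record a literal answerer who has disposed of everything, and section 8.1 keeps it that way. The disposal rate it yields is wrong for the sole primary outcome.

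The size of the error cannot be derived from the documents. If 25% and 45% are true rates and the loss is equal in both arms, losing 10% of disposers brings power to the 80% target when they count as not disposed. When they are dropped, about 20% must be lost to reach the same point. If the 25% was recorded through this script, the effect on power is smaller. The risk difference shrinks under equal loss, and further if kit users are lost more often, which is plausible because using the kit leaves no pills.

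**What to change.** Make these changes identically in both arms:

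1. Route a no at Q5 to Q9.
2. Follow a no at Q7 with one check: *Did you use all of them, or dispose of some?*
3. Amend the sentence in section 8.1 so that it permits this routing, and state in section 8.2 that both groups are asked.
4. In section 9, make the primary comparison between the concurrent arms. Count in the denominator all participants with unused tablets, including never-takers and those who disposed, and say how participants with no disposal answer are handled.
5. As a sensitivity check, compare the Q6 tablet count with the prescribed quantity, to flag patients who report no pills left but have tablets unaccounted for. This can flag a possible disposal but cannot prove one.

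The cost is a platform edit, an IRB modification and less direct comparability with the historical 25%.

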## **5. Study design**

### *5.1 Design*

This is a two-arm, randomized, controlled trial. The study will be conducted using an automated, remote text messaging platform (Way to Health) which delivers text messaging following orthopedic, neurosurgical, and urology procedures at the University of Pennsylvania.

The study team will identify potential participants from the electronic health record at the University of Pennsylvania Health System using Penn Data Store and Clarity, an EPIC reporting database. Patients undergoing a procedure in neurosurgery, orthopedics, or urology and who are prescribed an acute opioid will receive a text message four days following their discharge. This established system obtains remote, text-messaged based consent on post-operative day four. For those consenting, patients are queried on self-reported pain intensity, ability to manage pain, use of non-opioid analgesics, use of opioid analgesics, and opioid disposal. Once a participant responds and consents on day four, the participant will be mailed an opioid disposal kit which includes an informational sheet and the chemical packet (DispoRx).

Participants will be randomly assigned to intervention or control according to calendar week of surgery in alternating weeks over a 6-week period. Participants randomized to the control arm will receive no other interventions.

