### *5.4 Accrual*

We estimate that a sample size of 250 participants (125 per arm) will provide at least 80% power using a conservative Bonferroni adjustment of the Type I error rate with a 2-sided  $\alpha$  of 0.025 to detect a 20% change in disposal rates. Preliminary data suggest a baseline rate of 25%.

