## 147 **9. Analysis plan**

148 To compare sample characteristics between arms we will use t-tests or Wilcoxon rank-sum tests (F-tests or  
149 Kruskal-Wallis test) for continuous variables and Pearson chi square tests or Fisher's exact tests for categorical  
150 variables. In our primary analyses, we will compare rates of opioid disposal (baseline vs. 6-week study period).  
151 In the secondary analysis we will compare self-reported pain intensity, ability to manage pain, and opioid use.  
152 All hypothesis tests will be two-sided using a two-sided alpha of 0.025 as our threshold for statistical  
153 significance. We will use Stata and/or SAS to analyze the data.

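### The text-message script and section 8.2 disagree on whether a participant who answers No to disposal is asked again, and the primary outcome has no time point, so answers given before the kit is mailed may count

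*Supplement*

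**What the plan says.** Section 3.1 defines the endpoint in one sentence: "The primary outcome variable is rate of self-reported opioid disposal". Neither it nor section 9 gives a day of assessment, or says whether a participant's first, last, any or day-28 answer is used.

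On contact, section 8.2 says: "After providing informed consent, participants will be sent messaging on post-operative days 4, 7, 14, 21, and 28". It has the questions put at each of these times, with disposal asked of those who report no further use.

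The text-message script has its own branching. A participant with tablets left who plans to continue (Q8 = Yes) is told of a later check-in, and the script notes: "This patient will be texted in 1 week". One who does not plan to continue moves to Q9 on disposal. The No branch reads "If response = N or No → It's important to dispose of your unused medication", gives take-back information and asks one last question. The closing message at Q10 mentions no further check-in.

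On exposure, section 5.1 says: "Once a participant responds and consents on day four, the participant will be mailed an opioid disposal kit". Section 8.2 puts mailing within the first 7 days for orthopedics and urology and times it for day 21 in neurosurgery. Section 8.1 undertakes to leave the existing questions and message timing as they are.

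**The concern.** The kit is meant for people who have stopped opioids and still hold tablets. On day 4 such a person answers No at Q9, and that answer cannot reflect a kit that has not yet been mailed. Section 8.2 has the person asked again on day 7. The script, followed literally, states no further contact, so the pre-kit No would be the only disposal answer on record.

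With no time point in the endpoint, nothing excludes such answers under either text. In neurosurgery, the day-7 and day-14 answers also precede a kit timed for day 21.

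Answers given before exposure have the same expected distribution in both arms. Counting them as outcomes pulls the observed difference toward zero. If these participants are not asked again, no later analysis can recover what they did after the kit arrived.

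**Working it through.** **1. The two contact rules side by side**

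| Situation on day 4 | Section 8.2 | Script |
|---|---|---|
| Plans to continue opioid (Q8 = Yes) | Messaged again on days 7, 14, 21, 28 | Re-text stated, one week later |
| Stopped, not disposed (Q9 = No) | Messaged again on days 7, 14, 21, 28 | Last question; no re-text stated |
| Stopped, disposed (Q9 = Yes) | Messaged again on days 7, 14, 21, 28 | Last question; no re-text stated |

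The second row carries the problem. Under 8.2 the No is provisional; under the script as written it is final.

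**2. Reproducing the plan's power**

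Inputs: n = 125 per arm, a 25% baseline rate and a 20% change (section 5.4); two-sided alpha 0.025 (sections 5.4 and 9). I read 20% as percentage points, 25% to 45%. A relative reading, 25% to 30%, gives only 8.7% power and cannot be what was meant.

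Formula, with p̄ = (p1 + p2)/2:

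Power = Φ{ [ (p2 − p1)√n − z√(2p̄(1 − p̄)) ] / √(p1(1 − p1) + p2(1 − p2)) }, where z = 2.241 for two-sided 0.025.

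- (p2 − p1)√n = 0.20 × 11.180 = 2.236
- z√(2 × 0.35 × 0.65) = 2.241 × 0.6745 = 1.512
- √(0.1875 + 0.2475) = 0.6595
- Power = Φ(0.724 / 0.6595) = Φ(1.098) = 86.4%

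The plan claims that the sample "will provide at least 80% power", and it does. The minimum for 80% is 107 per arm, or 117 with continuity correction.

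**3. Dilution**

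Assumption: a share f of each arm has its outcome recorded before the kit can act, at the control rate, and the planned 20 points applies to everyone else. Then p2 = 0.25 + 0.20(1 − f). The documents do not give f, so a range is shown.

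| f | p2 | Observed difference (points) | Power, 125 per arm | n per arm for 80% |
|---|---|---|---|---|
| 0 | 0.45 | 20 | 86.4% | 107 |
| 5% | 0.44 | 19 | 82.6% | 118 |
| 10% | 0.43 | 18 | 78.1% | 131 |
| 20% | 0.41 | 16 | 67.6% | 163 |
| 30% | 0.39 | 14 | 55.3% | 210 |
| 50% | 0.35 | 10 | 30.2% | 398 |

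Power crosses 80% at f ≈ 8%, where p2 = 0.25 + 0.20 × 0.92 = 0.434.

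**4. Sensitivity to the rate among those affected**

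Suppose their recorded disposal rate is 5% (assumed) instead of 25%. At f = 30% the arms become 0.7 × 0.25 + 0.3 × 0.05 = 19% and 0.7 × 0.45 + 0.3 × 0.05 = 33%, and power is 61.2%. At f = 50% they become 15% and 25%, and power is 39.5%. The loss is somewhat smaller but still material.

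**The case against.** The strongest reply is that the script describes a single contact and section 8.2 governs how often it is repeated. The script never says that only continuing users are re-texted; that is inferred from its silence after Q9 and Q10. Its opening question tells patients that there may be several check-ins. The reply at Q8 speaks of a few days, which fits day 4 to day 7, and one week fits every later interval in 8.2. The first script question is not shown, and it may deal with contact frequency.

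Much of this stands, and it rules out several stronger readings that a reader might infer:

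- That the primary outcome is fixed on day 4. This follows only if the script governs, and section 8.2 says otherwise.
- That many participants are affected. No share of patients reaching Q9 on day 4 is given. The nearest figure, over 60% in section 4, counts tablets rather than patients, and by day 7.
- That continuing users are texted on days 11, 18 and 25. Those days appear nowhere in the documents.
- That the trial's real power is 55% or 30%. Those figures need an assumed share. They also assume that the planned 20 points is the effect among participants assessed after the kit, which section 5.4 does not say. If the 25% baseline came from the existing system's answers, the planned change might already be on the diluted scale.

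The objection does not remove the conflict. The script carries its own re-contact interval and attaches it to one branch only. Section 8.1 keeps the existing message timing, so the script may well be what participants receive. And even if 8.2 governs, the endpoint still has no time point that excludes pre-kit answers.

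**Conclusion.** The concern holds as an inconsistency combined with an undefined assessment time. Two facts are firm: the script and section 8.2 give different answers on whether a No is followed up, and the primary outcome does not say which answer counts. A day-4 answer necessarily precedes mailing, so pre-kit answers can enter the endpoint on either reading, more so in neurosurgery.

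Dilution is the consequence if the script governs, or if first answers are counted. Its direction, toward no effect, is clear. Its size is not known from the documents. The useful figure is the margin: under the assumptions above, the 80% power claim survives only while no more than about 8% of participants are affected. That margin is thin enough to settle the matter before enrolment. Confidence is high on the conflict and the missing time point, and only moderate on which text would apply in practice.

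**What to change.** 1. Reconcile the script with section 8.2. Participants who answer No at Q9 should keep receiving the scheduled messages until they report disposal or reach day 28, identically in both arms. Bring the one-week note under Q8 into line with the same schedule.
2. Define the primary outcome as disposal reported by day 28, using answers after the day-4 message.
3. Treat day-4 answers as baseline. State how participants who already report disposal on day 4 enter the denominator, with the same rule in both arms. Without this, the endpoint in item 2 leaves them undefined.
4. If the existing platform does not already re-text participants after a No, amend the statement in section 8.1 that message timing will not change, with whatever approval that needs.

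The cost is endpoint wording, a small change to platform logic and a few more automated texts to participants who have stopped opioids. No change in sample size follows from this point alone.
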